### 2.5. Sample Size

The primary outcome was the neonatal body temperature difference between KC prone position and KC lateral position. The sample size was calculated to achieve an 80% statistical power with an α of 0.05 to detect a 0.3 °C difference in the body temperature (DS 0.16) [5,13], and the non-inferiority margin was set at a 0.2 difference in body temperature [13]. In addition, we estimated a 10% loss to follow-up, so the sample size calculated is 35 participants in each group.

Additionally, the sample size was calculated to the secondary outcome; it was the difference in neonatal pain level between KC prone position and KC lateral position. With the same power an α to detect 0.83 points (DS 1), the non-inferiority margin was set at 1.53 points in PIPP-R, and we estimated a 10% loss, the sample size calculated is 29 participants in each group [5].

Given the scarce and heterogenous literature available on IVH [24], the populational behavior of this variable is unknown, with no references to calculate the sample size.

Therefore, the minimum estimated sample size to respond to the aims proposed is 35 subjects in each group.

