### 2.6. Randomization and Allocation

Participants will be recruited through non-probabilistic consecutive sampling.

Potentially eligible newborn patients will be identified in the research staff’s daily clinical practice or referred to them for eligibility assessment once they have been identified by clinicians who are not research staff.

Premature infants who meet all of the inclusion criteria and will be performing kangaroo care for the first time will be assigned to the experimental or control group on a simple 1:1 randomized basis, using a list of randomized numbers according to ID assignment from 1 to 70, using the random.org website.

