### 2.13. Statistical Analysis

Normality associated with each quantitative variable will be analyzed using the test Kolmogorov–Smirnov test.

A descriptive analysis will be performed of the demographic and clinical characteristics of subjects in both treatment groups: quantitative variables will be described by mean or median and their dispersion measurements, standard deviation or interquartile range, respective, as appropriate. Qualitative variables will be described by absolute frequencies and percentages. The descriptive analysis will be accompanied by the 95% confidence interval.

Prior to testing hypotheses, we will check whether both groups are homogeneous in terms of the baseline characteristics, using Student’s *t*-test or Mann–Whitney U for quantitative variables or ANOVA or Kruskal–Wallis if the variable does not follow normal distribution, and if statistically significant differences are found, we will continue with post hoc Bonferroni contrasts or weighted comparisons with Mann–Whitney U. Chi-squared will be used for qualitative variables.

If the groups are heterogeneous, confounding factors will be defined to adapt the final analysis to the main variable.

The effectiveness of KC modified lateral position compared to the KC conventional prone position will be assessed, calculating axillary temperature variation (Student’s t-test or Mann–Whitney U), level of pain (Student’s *t*-test or Mann–Whitney U), and IVH development (Chi-squared) in both groups.

Intention to treat (NNT) and protocol analyses will be performed. Should the results be conflicting, protocol deviations and/or breaches will be analyzed.

Safety analysis in relation to adverse events will be calculated using Pearson’s Chi-squared test or Fisher’s exact test as appropriate.

An explanatory model with stepwise linear regression will be created based on a significance level of 0.1, and confounding variables and their level of importance will be determined.

The statistical significance level will be *p* < 0.05. Data will be analyzed with the Statistical Package for the Social Sciences-IBM SPSS^®^ program version 25.0 (IBM, Chicago, IL, USA).

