## Figures and Tables

**Figure 1 ijerph-19-00293-f001:**
[figure not shown]
Flow of participants.

**Table 1 ijerph-19-00293-t001:** Participant timeline. SPIRIT Schedule of enrolment, interventions and assessment.

	Activity/Assessment	Staff Member	Approximate Time to Complete	Before First Session Kangaroo Care	t_0_	t_1_	t_2_	t_2_’	t_3_	t_4_	t_5_
enrollement	Informed consent	Study coordinator/study staff	10 min	x							
	Inclusion/exclusion form	Study coordinator/study staff	2 min	x							
	Allocation	Study coordinator/study staff	1 min	x							
Intervention	Intervention A: Prone kangaroo care	Neonatal nurse	5 min								
	Intervention B: Lateral Kangaroo care	Neonatal nurse	5 min								
	Eco-TF	physician	5–10 min	x							
Assessment	neonatal axillary temperature	Neonatal nurse	<1 min		x	x	x	x		x	
	Score pain	Neonatal nurse	min		x		x	x		x	
	Eco- TF: Intraventricular hemorrhage (IVH)	physician	5–10 min	x							x
	mother/father axillary temperature	Neonatal nurse	10 seg		x		x	x	x		
	Incubator temperature	Neonatal nurse	1.5 min		x					x	
	Incubator humidity	Neonatal nurse			x					x	
	Heater temperature	Neonatal nurse			x		x	x		x	
	Heart rate	Neonatal nurse			x		x	x		x	
	Oxygen Saturation	Neonatal nurse			x		x	x		x	
	Fio2	Neonatal nurse			x		x	x		x	
	Apnea				x		x	x		x	
	Box temperature	Neonatal nurse	1 min		x		x	x		x	
	Box humidity	Neonatal nurse			x		x	x		x	
	Sound	Neonatal nurse			x		x	x		x	
	Light	Neonatal nurse			x		x	x		x	
	Activity inside the box	Neonatal nurse	2 min		x		x	x		x	
	Duration kangaroo care	Neonatal nurse	<1 min								
	days in NICU stay	Study coordinator	5 min								x
	days in the hospital	Study coordinator	5 min								x
	days on mechanical ventilation	Study coordinator	5 min								x
	Mortality at 6 month old	Study coordinator	5 min								x

t_0_: 10 min previous the kangaroo care. t_1_: 15 min after beginning the kangaroo care. t_2_: 30 min after beginning the kangaroo care. t_2_’: if the duration kangaroo care is longer than 60 min, It assessment each 60 min after beginning the kangaroo care, so, 120 min after beginning the kangaroo care; 180 min after beginning the kangaroo care, etc. t_3_: at finish the kangaroo care. t_4_: 30 min after finish the kangaroo care. t_5_: delivery.

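### Pain is scored before kangaroo care, but the sized secondary pain comparison is unadjusted: valid and adequately powered at one-sided 5%, yet it gives up precision that a pre-specified baseline covariate would recover at no cost

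*Protocol article*

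**What the plan says.** - **Measurement.** Table 1 marks the pain score at t0, t2, t2' and t4. Its footnote defines the first of these as "t_0_: 10 min previous the kangaroo care", so a pre-session score is already collected.
- **Sizing.** Section 2.5 gives pain its own calculation: "With the same power an α to detect 0.83 points (DS 1"), and "the non-inferiority margin was set at 1.53 points in PIPP-R". The power and alpha carry over from the temperature calculation ("80% statistical power with an α of 0.05"). The result: "we estimated a 10% loss, the sample size calculated is 29 participants in each group". The trial as a whole takes the larger figure: "the minimum estimated sample size to respond to the aims proposed is 35 subjects in each group".
- **Allocation.** Section 2.6 assigns infants "on a simple 1:1 randomized basis", with no stratification described.
- **Analysis.** Section 2.13 names the test for "level of pain (Student’s *t*-test or Mann–Whitney U"). In the same sentence temperature is analysed as a variation, but pain only as a level.
- **Other adjustment clauses.** Section 2.13 provides for confounder adjustment if the groups prove heterogeneous, directed at the main variable. It also announces a stepwise explanatory regression at the 0.1 level, without naming its outcome. Section 2.14 promises a multivariable analysis to detect confounding or interaction. None of these names t0 pain.

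**The concern.** Pain relief is secondary aim (b) in Section 2.1, with a non-inferiority margin and a sample size, so the width of the interval for the pain difference matters. If an infant's score before the session predicts the score during it, a test that ignores the earlier score leaves explainable variation in the error term. The interval compared with 1.53 is then wider than it needs to be.

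The baseline is measured anyway. Section 2.13 also makes a positive choice of test here, so this concerns a stated method rather than a detail left to a later document.

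**Working it through.** **Inputs from the protocol (Section 2.5):** SD 1, expected difference 0.83, margin 1.53, power 80%, alpha 0.05 (sidedness not stated), loss 10%, 35 enrolled per group.

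**Assumed, because the documents do not give it:** the correlation r between the t0 score and the in-session score. SD 1 is taken as the SD of the level.

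**Step 1. Reproduce the protocol's pain sample size.**
Distance to the margin: 1.53 − 0.83 = 0.70.
n per group = 2 × SD² × (z₁₋α + z₁₋β)² / distance².
- One-sided 5%: 2 × (1.645 + 0.842)² / 0.49 = 25.2, so 26; 26 / 0.9 = 28.9, so **29**, as stated.
- One-sided 2.5%: 2 × (1.960 + 0.842)² / 0.49 = 32.05, so 33; 33 / 0.9 = 36.7, so 37, which does not match.

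The protocol's figure therefore implies one-sided 5%.

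**Step 2. Evaluable number.** 35 × 0.9 = 31.5, taken as 31 per group.

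**Step 3. Power without adjustment.** The standard error is √(2/31) = 0.254 and the non-centrality is 0.70 / 0.254 = 2.76. From the non-central t with 60 degrees of freedom, power is 86.0% at one-sided 5% and 77.4% at one-sided 2.5%.

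**Step 4. Power with t0 as covariate.** The residual SD is √(1 − r²), with one degree of freedom fewer.

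| r | Residual SD | Power, one-sided 5% | Gain (points) | Power, one-sided 2.5% | Gain (points) |
|---|---|---|---|---|---|
| 0.2 | 0.980 | 87.2% | 1.2 | 79.0% | 1.6 |
| 0.3 | 0.954 | 88.7% | 2.7 | 81.1% | 3.7 |
| 0.4 | 0.917 | 90.8% | 4.8 | 84.1% | 6.7 |
| 0.5 | 0.866 | 93.3% | 7.3 | 87.9% | 10.5 |
| 0.7 | 0.714 | 98.5% | 12.5 | 96.7% | 19.3 |

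**Step 5. Would a change score do instead?** The SD of a change from t0 is √(2(1 − r)) times the SD of the level: 1.18 at r = 0.3, 1.00 at r = 0.5 and 0.77 at r = 0.7. It loses precision below r = 0.5 and gains nothing at 0.5. The gain comes from using t0 as a covariate, not from subtracting it.

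**The case against.** **The planned test is not wrong and not underpowered.** This stands. A t-test between randomised arms has correct type I error. At the one-sided 5% that reproduces the 29, its 86% power exceeds the 80% target because temperature, not pain, sets the enrolment.

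**The gain rests on a correlation nobody has stated.** This also stands. Section 2.11 describes PIPP-R as valid during painful procedures, and procedures and analgesia are recorded for each session. In-session scores may follow events in the session more than the state ten minutes before it. At r of 0.2 to 0.3 the gain is only about 1 to 4 points.

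**Larger losses may be inferred.** A loss near 12 points at r = 0.5 appears only with 26 evaluable per group and one-sided 2.5% (69.7% against 81.5%). The protocol enrols 35, and its 29 does not reproduce at that level.

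**A reader might infer that the unadjusted comparison misses pain alleviation, or is biased by chance baseline imbalance.** Neither follows. Under randomisation the unadjusted difference and the linear ANCOVA coefficient target the same mean difference between arms, and the unadjusted interval already allows for chance imbalance.

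**A reader might infer that pain can never be adjusted.** That is too strong. The stepwise and multivariable analyses do not exclude pain. They simply do not fix t0 pain in advance, so they do not replace a pre-specified covariate.

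**Covariates for a secondary outcome belong in the SAP.** This would answer a silent protocol, but Section 2.13 names the test.

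**The t0 score is not a perfect baseline.** Table 1 places allocation before the first session, nursing staff know the group (Section 2.7), and the Discussion concedes that pain observers cannot be blinded. This is a small caveat that calls for a sensitivity analysis.

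**Conclusion.** The point holds as a matter of efficiency. The protocol collects a pre-session pain score and then specifies a pain comparison that does not use it. At 31 evaluable per group, the power given up is about 1 to 7 points at one-sided 5% for r between 0.2 and 0.5, and about 12 at r = 0.7. At one-sided 2.5% the figures are about 2 to 10, and 19.

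These rest on the protocol's SD of 1 applying to the level, on approximate normality (Section 2.13 allows for a rank test) and on an assumed r. They also assume that outcome and baseline come from the same session, because a first-session t0 score need not correlate to this degree with scores days later. This is a free improvement to a sized secondary analysis. It is not an error of validity or of what is being estimated.

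**What to change.** In Section 2.13, replace the unadjusted pain test with a pre-specified ANCOVA:

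- **Outcome:** PIPP-R score in the first session at one fixed in-session time point, for example t2 (30 minutes after the start).
- **Terms:** randomised position, and the first-session t0 PIPP-R score as a fixed covariate, kept whatever the observed balance.
- **Decision:** compare the confidence limit for the adjusted lateral-minus-prone difference with 1.53, at a stated one-sided level.
- **Sensitivity:** report the unadjusted difference with its interval, because t0 is scored after allocation by unblinded staff.

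Outcome and covariate must come from the same session. Table 1 repeats both the t0 and in-session scores at each session, and only the first-session t0 precedes all kangaroo care.

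The cost is a few lines of analysis text, with no extra infants or measurements. If t0 turns out to be uninformative, the covariate costs one degree of freedom, a loss of less than 0.1 points of power at 31 per group.

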Meanwhile, the rate of IVH stands at around 20–38% in children under 28 weeks of gestational age (GA) and is more frequent in the first 72 h of life [19,20]. Thus, the risk of bleeding is inversely related to gestational age and can be attributed to three factors: vascular immaturity of the germinal matrix, deficient extravascular matrix, and cerebral blood flow alterations. In conventional kangaroo care prone position to a premature infant, the head is turned 90 degrees, compressing the internal jugular vein and therefore compromising venous blood drainage. This potential venous congestion leads to increased intracranial pressure, reduced brain oxygenation, and ultimately of the germinal matrix, thus increasing the risk of IVH [21]

KC is a neuroprotective intervention that can improve survival in premature infants [14], becoming the star program at neonatal units around the world; this is the reason to recommend it as soon as it is possible, and for as long time, requiring postural changes of the neonate towards the KC lateral position if KC is prolonged [22,23].

Although some studies have proposed that premature infants with lateral head position have poorer cerebral vascular flow, cerebral oximetry, and greater risk of IVH, evidence of this is scarce and low quality [24]. Thus, recommendations in clinical practice are variable; on occasions, preterms under 28 weeks of GA should be positioned with the head in the midline position for at least the first 72 h and up to the first seven days of life, and with the incubator inclined 15–30 degrees [24,25,26]. This would entail placing extremely premature in the modified KC lateral position during the first 7 days of life, lying on the bare thorax or chest of the mother or father, with the limbs flexed towards the midline and the head neutral and in line with the rest of the body. However, there is no evidence of the effectiveness of modified KC lateral position in relation to thermal. One side lying position could be a thermoregulation challenge, compared with prone position, because there is less skin surface in contact with the skin of the kangaroo provider.

There is no evidence either on hemodynamic stability and the consequences on pain or stress during one side lying position KC.

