The following independent variables will be obtained from each participant in every KC session:Demographic variables: gestational age at birth, gender, and birth date.Clinical data: Apgar score (test to assess the extrauterine adaptation of the newborn 1, 5, and 10 min after birth), type of delivery (eutocic, instrumental, cesarean), birth weight, gestational age, actual weight, hours of life, pathology at five days of life, analgesia administered (drug, route, dose and time since the last dose), painful/stressful procedures during kangaroo session, respiratory support (support type and fraction of inspired oxygen).Hemodynamics-related: maximum heart rate and minimum peripheral oxygen saturation observed for 20 s, apneas. Continuous hemodynamic monitoring to measure the heart rate, peripheral oxygen saturation, and apnea with Philips IntelliVue MP60/MP70^®^ monitor (Koninklijke Philips Electronics N.V., Eindhoven, Netherland) or Masimo SET^®^ oximetry monitor (Masimo, Irvine, CA, USA).Temperature-related: Giraffe ^®^ (GE Healthcare, Chicago, IL, USA) incubator air temperature and humidity; temperature and humidity of room or open-bay setting, where neonate is located assessed by Multi-Function Environment Meter PCE EM882 (PCE, Durham, United Kingdom), and temperature of humidifier chamber Dräger VentStar^®^ (Dräger, Lubeca, Germany).Kangaroo care: position (prone or lateral), date of KC session, session number, duration, KC provider (mother/father), axillary temperature of KC provider, materials used for kangaroo care, person transferring neonate.Environment room or open-bay setting: light and sound in macroenvironment assessed by Multi-Function Environment Meter PCE EM882, and activity inside the box room or open-bay setting with scale NIDCAP Nursery Certification Program [32].Adverse events or incidents: accidental removal of the line, such as umbilical venous or arterial catheters, venous catheter, or endotracheal tubes.The long-term outcomes we have collected are the number of days in NICU stay, the total number of days in the hospital, the number of days on mechanical ventilation, and mortality.The patient’s medical history will be used for the collection of demographic, clinical, and intraventricular hemorrhage (IVH)-related data. And the direct observation for measuring pain, activity inside the room or open-bay setting, and rest of outcome. They will be extracted and transferred to the data collection notebook.

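### IVH is compared by an unadjusted Chi-squared test although gestational age, which the protocol itself calls prognostic, is recorded: prespecifying it as the one covariate is a free, modest improvement

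*Protocol article*

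**What the plan says.** Section 2.13 names the between-group test for IVH as "IVH development (Chi-squared) in both groups" and attaches no covariate to it. The Introduction states that "the risk of bleeding is inversely related to gestational age" and that "the rate of IVH stands at around 20–38% in children under 28 weeks of gestational age"; it gives a direction for the age effect but no coefficient. Section 2.11 lists "gestational age at birth, gender, and birth date" among the variables recorded for each infant. Section 2.6 says that infants "will be assigned to the experimental or control group on a simple 1:1 randomized basis"; no stratification by gestational age is stated.

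Three other clauses bear on adjustment:
- In 2.13, if the baseline tests find the arms heterogeneous, "confounding factors will be defined to adapt the final analysis to the main variable". Section 2.10 makes axillary temperature the primary outcome.
- 2.13 also plans an explanatory stepwise linear regression with a 0.1 significance level. No outcome is named.
- 2.14 plans a general multivariable analysis to look for confounders and interactions. It names neither IVH nor gestational age.

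**The concern.** The protocol identifies one strong baseline predictor of IVH and collects it, but uses it in neither the allocation nor the IVH comparison. If chance leaves one arm younger, the crude comparison mixes an age effect with the effect of position, and the reader has no prespecified analysis that separates them. IVH is one of the two secondary aims in 2.1, so a misread difference in either direction would matter. A covariate chosen after the data are seen would carry less weight than one fixed now.

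**Working it through.** **1. The plan's own figure.** No sample size is given for IVH; 2.5 says there was no basis for one. The 35 per group comes from temperature. Taking the 0.1 °C gap between the two figures in 2.5 (0.3 and 0.2), SD 0.16, one-sided 0.05 and 80% power: n = 2 × (1.645 + 0.842)² × 0.16² / 0.1² = 31.7, so 32. Then 32 / 0.9 = 35.6, close to the stated 35.

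**2. What 35 per arm gives for IVH.** For 38% vs 20% (the ends of the protocol's range), two-sided 0.05, with mean rate 0.29:
- Null term: 1.96 × √(2 × 0.29 × 0.71) = 1.258. Alternative SD: √(0.38 × 0.62 + 0.20 × 0.80) = 0.629.
- Power = Φ[(0.18 × √35 − 1.258) / 0.629] = Φ(−0.307) = 0.38.
- For 80% power: (1.258 + 0.842 × 0.629)² / 0.18² = 98.6, so 99 per arm.

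**3. How often the arms differ in age.** Assumption, not in the documents: SD 1.3 weeks (23 to 27 completed weeks). The standard error of the difference in means is 1.3 × √(2/35) = 0.311 week.
- P(difference ≥ 0.5 week) = P(|Z| ≥ 1.61) = 0.11, about 1 trial in 10.
- P(difference ≥ 0.4 week) = P(|Z| ≥ 1.29) = 0.20.

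**4. What that does to IVH.** Assumptions: overall IVH 29% (midpoint of 20–38%), no position effect, odds ratio per extra week 0.8 to 0.5. Given a gap of at least 0.5 week, its mean size is 0.311 × φ(1.61)/P(Z > 1.61) = 0.311 × 2.03 = 0.63 week. The shift is then roughly 0.29 × 0.71 × 0.63 × |ln OR|. The simulated columns come from 4,000 trials per row (70 infants, simple randomization) and are restricted to trials with a gap of at least 0.5 week. Adjusted means a logistic likelihood-ratio test with gestational age.

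| OR per week | Shift, formula (points) | Shift, simulated (points) | False positives, Chi-squared | False positives, adjusted |
|---|---|---|---|---|
| 0.8 | 2.9 | 2.9 | 6.7% | 7.6% |
| 0.7 | 4.6 | 4.6 | 6.5% | 6.0% |
| 0.6 | 6.6 | 6.4 | 8.8% | 5.4% |
| 0.5 | 9.0 | 8.4 | 10.3% | 4.8% |

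Each error rate rests on about 400 trials, so its standard error is 1.1 to 1.5 points. Over all trials, balanced or not, Chi-squared error was 0.044 to 0.054 (8,000 trials per setting).

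**5. Power, like for like.** Likelihood-ratio tests without and with gestational age, 35 per arm:

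| IVH rates | OR 0.8 | OR 0.7 | OR 0.6 | OR 0.5 |
|---|---|---|---|---|
| 38% vs 20% | 0.408 → 0.403 | 0.403 → 0.410 | 0.401 → 0.425 | 0.399 → 0.443 |
| 29% vs 14.5% | 0.329 → 0.334 | 0.322 → 0.332 | 0.319 → 0.346 | 0.321 → 0.362 |
| 38% vs 10% | 0.823 → 0.826 | 0.827 → 0.835 | 0.826 → 0.852 | 0.828 → 0.863 |

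Across all settings run, including larger position effects, the gain is about 0 to 6 points.

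**6. Would the baseline check catch it?** A t-test on 68 degrees of freedom is significant only beyond 1.995 × 0.311 = 0.62 week, which happens in 5% of trials. Of gaps of 0.4 week or more, 1 − 0.05/0.20 = 75% go unflagged; of gaps of 0.5 week or more, 1 − 0.05/0.11 = about 55%.

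**7. Events available.** 70 × 0.20 = 14 to 70 × 0.38 = 27. Section 2.11 plans an ultrasound before the first session to identify earlier bleeding, so new bleeds may be fewer.

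**The case against.** Randomization alone makes the Chi-squared test valid, and an unadjusted comparison of a secondary outcome is an accepted choice. That stands. A reader might infer that the planned test is biased or has inflated error; it does not, because the inflation in step 4 exists only within the imbalanced trials and averages out over all of them.

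A reader might also infer that a harmful imbalance is likely. At about 1 in 10 it is not, and the resulting 3 to 8 points are smaller than the sampling error of the IVH difference itself, √(2 × 0.29 × 0.71 / 35) = 10.8 points.

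The size of the benefit rests on a slope that the documents do not give. At an odds ratio of 0.8 per week, adjustment did not lower the conditional error. This also stands and is why a range is shown.

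Section 2.14 rules out saying that IVH could never be adjusted under this protocol, and an analysis plan not shown might add detail. But 2.14 is too general to count as a prespecified IVH adjustment, and 2.13 does fix a covariate-free test.

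Finally, it is tempting to tie this to the stopping looks in 2.15. That section names no test for them, and an edit to 2.13 would not change them.

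**Conclusion.** The point holds as a modest improvement that costs nothing. The protocol names and records a prognostic factor for IVH, randomizes without stratifying on it, and then fixes a test that ignores it. The routes to adjustment in 2.13 and 2.14 do not fill the gap: one depends on a significance test and concerns temperature, one is a linear model for what is a yes/no outcome, and one is generic.

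The consequence is a possible misreading in the minority of trials with an age imbalance. It is clear only if the age slope is steep (odds ratios of about 0.6 to 0.5 per week) and negligible at 0.8. Adjustment does not rescue power: 38% vs 20% stays near 0.40 to 0.44. All of this assumes the 1.3-week SD, the 20–38% rate and the stated slopes. The calculations tested the logistic likelihood-ratio test, not the interval for the marginal risk difference proposed below.

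**What to change.** In 2.13, replace the IVH test by a logistic model with position and gestational age at birth (in weeks) as the single prespecified covariate, reported as a marginal risk difference with 95% CI. Apply it whatever the baseline tests show, and keep the crude Chi-squared test as descriptive. Add that new bleeds after the first ultrasound may be fewer than the 20–38% rate implies, so no further covariates will be entered.

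The cost is one or two sentences. No new data are needed, and the sample size and the conduct of the trial do not change.

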### 2.2. Design

The study is designed as a non-inferiority randomized parallel clinical trial.

The CONSORT guidelines for randomized controlled trials will be used. This protocol also adheres to the SPIRIT guidelines (Supplementary Materials: checklist SPIRIT).

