### 2.15. Monitoring

An interim analysis is performed on the primary endpoint when 20% of patients have been randomized. The idea is to be able to identify an increase in HIV incidence in the control group, such as other potential hazard events in all participants. In that case, the study would come to a halt. The main investigator will have unblinded access to data and will discuss the results of the interim analysis with the research team.

The trial will not be stopped in case of futility related to the outcome variables because kangaroo care is the current intervention in the neonatal units due to clinically proven benefits, so futility is not sustainable.

The main investigator has the ultimate authority to stop or modify the trial and to ensure the protocol’s continued. He will follow up with all participants, and he will check all kangaroo care sessions are completed as it is referred to in the protocol. If that is not the case, the session will be discarded.

Changes on the protocol will be notified to all team members immediately and keeping all documentation standardized. All updated versions will be available in a digital form, and team members will be noticed during practical and theoretical lectures.

Safety and complications were monitored by identifying kangaroo potential adverse events noted down in the Data Collection Logbook (DCL), such as hypothermia, continuous hemodynamic instability during kangaroo care, or accidental displacement of any therapeutic device. Those events will be collected and analyzed in the first 24 h by the investigator in charge of the session, notifying the main investigator. The main investigator will record this adverse event on the study database, taking the actions required according to the severity and impact.

A committee in charge of data monitoring has not been created, the tracking is carried out by the research team. Non-audits have been scheduled.

Preliminary analyses every 20 new participants will be done to discard a rising HIV incidence in the control group, which would mean the study would come to a standstill.

Established withdrawal criteria are hypothermia or a Kangaroo care session less than 60 min.

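### The rule for conflicting intention-to-treat and per-protocol results gives no non-inferiority verdict, and temperature-dependent removals are not tied to either analysis set

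*Protocol article*

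**What the plan says.** Section 2.2 sets the design: "The study is designed as a non-inferiority randomized parallel clinical trial". Section 2.5 adds that "the non-inferiority margin was set at a 0.2 difference in body temperature".

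Section 2.13 names two analysis sets, "Intention to treat (NNT) and protocol analyses will be performed", and then deals with disagreement between them: "Should the results be conflicting, protocol deviations and/or breaches will be analyzed". It names neither set as primary and does not require both to succeed. It does not say what a disagreement means for the claim, and no other section does.

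Sections 2.4 and 2.15 list hypothermia and a kangaroo care session shorter than 60 minutes as grounds for removal or withdrawal. Section 2.15 also has the main investigator check that every session followed the protocol, and adds: "If that is not the case, the session will be discarded". Neither section says whether these removals apply to the per-protocol set, to the intention-to-treat set or to both.

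**The concern.** A non-inferiority trial needs its verdict fixed before the data are seen. Here the plan foresees that the two sets may disagree, but answers with a review of deviations that begins once both results are known. Nothing written prevents the claim from then resting on whichever set met the margin.

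The removal criteria make this sharper. Axillary temperature is the primary outcome, and hypothermia is a low value of it. Under section 2.8, a temperature that stays below 36.5 °C also ends the session, which can bring it under 60 minutes. If the lateral position is colder, these criteria take more infants or sessions out of the lateral arm than the prone arm and narrow the observed difference. The introduction itself says that side-lying might challenge thermoregulation because less skin is in contact. At stake is a claim that lateral care is no worse for temperature when it is worse by the full margin.

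**Working it through.** **1. The plan's own figure and its error rate.** Inputs from section 2.5: power 80%, α 0.05, difference 0.3 °C, SD 0.16, margin 0.2 °C, 10% loss.

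n per arm = 2 × [SD × (z_α + z_β) / |0.3 − 0.2|]²

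With one-sided α = 0.05: 2 × [0.16 × (1.645 + 0.842) / 0.1]² = 31.65. Dividing by 0.9 gives 35.2, which matches the stated 35 per group. One-sided 0.025 gives 41, or 46 after loss, and does not match. So the sample size implies a 5% one-sided error rate. A conventional two-sided 95% interval would imply 2.5%. Both are shown below. (Whether an assumed difference larger than the margin makes sense is a separate question.)

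**2. Effect of the open conflict rule alone.** Simulation of 20,000 trials: 35 per arm, SD 0.16, true lateral deficit exactly 0.2 °C, so every declaration of non-inferiority is false. Per-protocol exclusions are random. The exclusion rates are assumptions.

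| Excluded | Either set, 5% level | Both sets, 5% level | Either set, 2.5% level | Both sets, 2.5% level |
|---|---|---|---|---|
| 10% | 6.2% | 3.5% | 3.1% | 1.6% |
| 20% | 6.8% | 3.0% | 3.5% | 1.4% |
| 30% | 7.2% | 2.5% | 3.9% | 1.4% |

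Taking the claim from either set adds about 1 to 2 points.

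**3. Effect of removing infants below 36.5 °C.** The prone mean is not in the article, so it is varied. For an arm with mean μ, let a = (36.5 − μ)/0.16. The fraction removed is Φ(a), and the mean of those left rises by 0.16 × φ(a)/(1 − Φ(a)).

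Example, prone mean 36.9 °C and lateral mean 36.7 °C:
- Lateral: a = −1.25, about 10.6% removed, mean rises by 0.033 °C.
- Prone: a = −2.5, about 0.6% removed, mean rises by 0.003 °C.
- Difference left: 0.200 − 0.033 + 0.003 = 0.170 °C.

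A true deficit at the margin therefore looks smaller than the margin. The same calculation leaves 0.189 °C at a prone mean of 37.0 °C and 0.140 °C at 36.8 °C.

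Simulated false non-inferiority, 35 per arm:

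| Prone mean | Removed, prone / lateral | Full set, 5% level | Truncated set, 5% level | Full set, 2.5% level | Truncated set, 2.5% level |
|---|---|---|---|---|---|
| 37.0 °C | 0.1% / 3.0% | 5.1% | 8.8% | 2.6% | 4.7% |
| 36.9 °C | 0.6% / 10.5% | 5.1% | 20.0% | 2.3% | 11.9% |
| 36.8 °C | 3% / 26.6% | 4.8% | 50.8% | 2.6% | 38.2% |

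With 31 per arm (35 × 0.9 = 31.5) at the 2.5% level, the truncated set gives about 3.1% at 37.1 °C, 4.0% at 37.0 °C, 11% at 36.9 °C and 35% at 36.8 °C, against about 2% in the full set.

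**4. What a both-sets rule achieves.** If the removals touch only the per-protocol set, requiring both sets returns the rate to about 5% (or 2.5%), because the full set then limits the claim. If they touch both sets, the two sets are truncated alike and the truncated columns apply whatever the conflict rule says. So the definition of the intention-to-treat set matters as much as the rule.

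**The case against.** The strongest reply is that this is mostly an omission. Planning both analyses and promising to look at deviations is neither false nor contradictory, and naming the decisive set is often left to an analysis plan that is not at hand. In part that stands: a reader might infer that the more favourable set will decide, and the article does not say so. But it does state a rule for conflict, and that rule yields no verdict.

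Other stronger readings also go further than the text:
- A reader might take the larger rates in step 3 as the effect of the conflict rule. They come from temperature-dependent removal. The rule's own effect is step 2, and at the 2.5% level even an either-set claim (3.1–3.9%) stays below 5%.
- A reader might conclude that conflicts will be common and mostly favour the claim. That holds only for cool prone means. Section 1 gives normothermia as 36.5–37.5 °C, and at its midpoint of 37.0 °C the inflation is modest. At a prone mean of 36.7 °C the lateral mean would be 36.5 °C and half of that arm would be removed, far from the planned 10% loss.
- A reader might assume that only the per-protocol set is truncated, or that sessions in the other position dilute the intention-to-treat set. The article ties the removals to no set and describes no such sessions; section 2.8 says allocation is maintained.

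The simulation is also simpler than the protocol. It uses one value per infant and removes on a single low reading. Section 2.8 suspends care only after repeated low readings, infants may have several sessions, and hypothermia as a removal criterion is not given a threshold.

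Finally, section 2.7 blinds those who process and analyse the data. That safeguard is real but partial: section 2.15 gives the main investigator, who also checks the sessions, unblinded access to data in the context of the interim analysis, and section 2.12 gives the lead researcher sole database access.

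**Conclusion.** The concern holds in a limited form. The conflict rule leaves the non-inferiority verdict undetermined, and the removals for hypothermia or short duration are not assigned to an analysis set. Any set that applies the hypothermia removal is biased toward non-inferiority if lateral care is truly colder.

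The direction of that bias follows from the text; its size does not. The open rule alone costs about 1 to 2 points of error. The removals cost anything from very little (3–4% against 2.5% at prone means of 37.0–37.1 °C) to a great deal (35% at 36.8 °C). These figures assume SD 0.16, a true deficit equal to the margin, and removal of any infant below 36.5 °C. The article does not show that the favourable set would be chosen or that conflicts would be frequent.

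**What to change.** Replace the conflict sentence in section 2.13 with a rule that decides, and align sections 2.4 and 2.15 with it:

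- The intention-to-treat set contains all randomised infants by allocated position, with all their sessions, including those stopped for low temperature or lasting under 60 minutes.
- The per-protocol set is defined before unblinding, from deviations that do not depend on temperature.
- Non-inferiority is concluded only if the confidence limit for the temperature difference lies within the 0.2 °C margin in both sets. The confidence level should be stated, because section 2.13 does not link its tests to the margin.
- If the sets disagree, non-inferiority is not shown, and the deviation analysis is descriptive.

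This concerns which data are analysed and leaves the handling of a cold infant during a session unchanged. Naming one primary set would also make the verdict determinate, but it protects against the removal bias only if that set keeps all infants and sessions.

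The cost is wording, plus some loss of power because both sets must succeed; that loss has not been calculated. The planned 35 per group need not change on this account if evaluable losses stay within the planned 10%.
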